### Data management and monitoring

Participants’ data will be identified only by a study number (starting with 001) and only the principal investigator and study coordinator will have access to identifiers that can link the data to the individual participant. Participants who drop out will be noted and their reasons documented. Data will be entered and stored on a standalone computer into excel and SPSS data files, and the information will be password protected. We will assure the quality of data entry by random checking of the data entered. Study data is only accessible by the researchers involved in the trial, and only the principal investigator and investigators in the project will have access to the data for analysis. The investigators will monitor that the informed consent process is conducted appropriately and that informed consent was obtained prior to proceeding with any study procedures. Only participants who meet study eligibility criteria will be enrolled. Data will be kept for 10 years after the research is completed and all data (electronic and hard copy) will be destroyed after the storage period. There is no data monitoring committee due to the characteristics of the current study.

### Data analyses plan

All outcome variables will be checked for normality and results will be expressed as mean and standard deviation (SD) or median and ranges. Multiple regression analyses will be performed to examine the potential independent predictors of T2D risk. At baseline, differences in continuous variables between groups (control group vs. exercise group) will be analyzed by Student’s *t* test or the Mann-Whitney *U* test, as appropriate. Differences in categorical variables at baseline between the two groups will be explored by chi-squared tests. Repeated-measured analysis of variance will be used to assess the effect of exercise (time (pre-post 22-weeks’ intervention) × group interactions) on the primary (insulin resistance) and secondary study (adiposity, ectopic fat, cardiorespiratory fitness, cardiovascular disease risk factors, inflammation markers, etc.) outcomes and the intention-to-treat principle will be applied. For sensitivity analyses, we will analyze the effect of the adherence to the program on the results of the intervention.

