#### Sample size calculation

Insulin resistance is the primary outcome of this study. We expect that pre-post intervention differences in our design consisting in two experimental groups, control and exercise group, will have a size effect (Cohen’s *d*) of 0.7 for insulin resistance (i.e., homeostatic model assessment, HOMA) (*N* = 34 in each group, 80% power and *α* of 0.05). These effect size estimates are based on previous studies performed in overweight children with similar age range and a with intervention programs including supervised exercise [33, 43, 44]. We observed in one previous study, in which the effect of the same intervention program was tested on hepatic fat in overweight/obese children, losses to follow-up of approximately 7% (data not shown). Previous studies have reported losses to follow-up of between 4 and 17%. Assuming a maximum loss of follow-up of 20%, we decided to recruit a total of 84 children (50% girls), 42 children for each group.

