### Outcome measures for the first objective

IRS and the risk of T2D is characterized by excess adiposity, low levels of insulin sensitivity, dyslipidemia and hypertension. In the current project, the primary outcome is insulin resistance. Secondary outcome variables include total, abdominal and visceral adiposity, ectopic fat (hepatic and pancreatic fat), cardiorespiratory fitness, cardiovascular disease risk factors and inflammation markers, hepatokines and adipokines (Table 2). Primary and secondary outcomes will be evaluated at baseline and repeated after 22 weeks of intervention (Fig. 2). Post-intervention measurements will be scheduled within 3 days following the last healthy lifestyle program session or exercise session in the control or in the exercise group, respectively.

**Table 2 Tab2:** Summary of the methodology of primary and secondary outcome measurements and potential confounders in the PREvention of DIabetes in KIDs (PREDIKID) study

Measure	Methodology
Primary outcomes	
Insulin resistance	Homeostatic model assessment (HOMA), biochemical analyses
Expression of miRNA in circulating exosomes and white blood cells	RNA-seq methodology
Secondary outcomes	
Physical measures	
Body mass (kg)	Scale
Height (cm)	Stadiometer
Waist circumference (cm)	Non-elastic tape
Blood pressure (mmHg)	Oscillometric monitor device
Body fat (%)	Dual X-ray absorptiometry
Abdominal adiposity (g)	Dual X-ray absorptiometry
Visceral abdominal adiposity (cm^2^)	Magnetic resonance imaging
Hepatic fat (%)	Magnetic resonance imaging
Pancreatic fat (%)	Magnetic resonance imaging
Carotid intima medial thickness (mm)	Doppler ultrasonography
Biochemical measures	
Glucose (mg/dL)	Enzymatic spectrophotometry
Insulin, leptin, adiponectine, fetuin-A, FGF21	Enzyme-Linked Immunosorbent Assay
Hemoglobin A1c	Enzymatic tests
Total cholesterol, HDL- and LDL-cholesterol (mg/dL)	Enzymatic spectrophotometry
Triglycerides (mg/dL)	Enzymatic spectrophotometry
Alanine aminotransferase (U/L)	Enzymatic tests
Aspartate aminotransferase (U/L)	Enzymatic tests
Gamma glutamyl transferase (U/L)	Enzymatic tests
C-reactive protein (g/dL)	Enzyme immunoassay
TSH, T3, T4	Radioimmunoassay
Uric acid (mg/dL)	Enzymatic spectrophotometry
Urea, bilirubin	Enzymatic spectrophotometry
Cardiorespiratory fitness	20-m shuttle run test Cardiopulmonary exercise test
Dietary assessment	24-h recalls and food frequency questionnaires
Physical activity assessment	Accelerometry and questionnaires

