Sleeping habits	Accelerometry and questionnaires
Sedentary behaviors	Questionnaires
Potential confounders	
Pubertal development (Tanner stage)	Physical examination
Sociodemographic variables	
Socioeconomic status	Questionnaires
Neonatal variables	Health booklets and questionnaires
Family medical history	Questionnaires
Demographic characteristics	Questionnaires

*PREDIKID* Prevention of Diabetes in Kids; *FGF21* fibroblast growth factor 21; *HDL* high-density lipoprotein; *LDL* low-density lipoprotein; *miRNA* micro RNA; *TSH* thyroid stimulating hormone; *T3* triiodothyronine; *T4* free thyroxine

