### Confounding variables

#### Puberty stage

At baseline, the pediatrician will evaluate Tanner staging by direct-examination breast palpation in girls and testicular measurement by orchidometer in boys.

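### The time × group repeated-measures ANOVA on two visits is a change-score t test: valid and adequately sized, but less efficient than ANCOVA on the baseline value

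*Protocol article*

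**What the plan says.** The Data analyses plan of the protocol article names the method for the treatment effect: "Repeated-measured analysis of variance will be used to assess the effect of exercise". The quantity tested is the interaction: "time (pre-post 22-weeks’ intervention) × group interactions) on the primary (insulin resistance) and secondary study" outcomes. No covariate is named for this model. The multiple regression in the same section looks for predictors of T2D risk and does not estimate the treatment effect.

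There are two visits (Outcome measures for the first objective): "Primary and secondary outcomes will be evaluated at baseline and repeated after 22 weeks of intervention".

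The Sample size calculation is on the same footing: "We expect that pre-post intervention differences in our design consisting in two experimental groups, control and exercise group", with an effect size "of 0.7 for insulin resistance (i.e., homeostatic model assessment, HOMA"). It gives 34 per group at 80% power and α 0.05, raised to 42 per group for up to 20% loss to follow-up. It does not say which SD standardises d.

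Table 2 lists "Pubertal development (Tanner stage") among the potential confounders, and the Puberty stage section says how it is obtained: "At baseline, the pediatrician will evaluate Tanner staging by direct-examination breast palpation in girls". Sex is recorded under Sociodemographic variables.

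**The concern.** With one pre and one post value per child, the time × group test reduces to comparing mean change between arms. A change score uses the baseline value but sets its coefficient to 1. When the true within-group slope is below 1, as it is with equal SDs and r < 1, subtracting the whole baseline puts noise into the comparison.

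Two things follow. The treatment effect is estimated less precisely than the same data allow. And if the arms differ in mean baseline HOMA by chance, the change-score estimate is shifted by regression to the mean: the arm that starts higher is expected to fall further without any treatment effect. In a trial of this size, both are worth avoiding when the remedy is a change of wording.

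**Working it through.** **Inputs from the article.** d = 0.7, 34 per group, 80% power, α 0.05, 42 per group recruited (Sample size calculation); two visits (Outcome measures for the first objective); time × group test without covariates (Data analyses plan).

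**Assumed.** Two-sided α; d standardised by the SD of the change score; equal SDs at both visits; r, the correlation of baseline with week-22 HOMA, from 0.3 to 0.9. The article gives none of these.

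**1. The plan's own figure.** For d = 0.7, two-sided 0.05 and 80% power, the normal approximation gives 33 per group and the noncentral t gives 33.02, rounded up to 34. Power at 34 is 81.2%. A one-sided test would need only 26, so the two-sided reading is the one that fits. The stated 34 reproduces.

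**2. Identity of the tests.** On one simulated data set with 34 per group, the interaction F was 4.0993 and the squared change-score t was 4.0993.

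**3. Variance ratio.** Let σ0 and σ1 be the SDs at baseline and week 22.
- Change score: σ0² + σ1² − 2rσ0σ1
- ANCOVA: σ1²(1 − r²)
- Difference: (σ0 − rσ1)², which is never negative

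So the direction does not need equal SDs; the size does. With σ0 = σ1 the ratio of ANCOVA to change-score variance is (1 − r²)/(2(1 − r)) = (1+r)/2.

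**4. Power at 34 per group.** The effective d for ANCOVA is 0.7/√((1+r)/2). Power comes from the noncentral t with 65 df (baseline as the only covariate).

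| r | Variance ratio | Effective d | ANCOVA power | n per group for 80% |
|---|---|---|---|---|
| 0.3 | 0.65 | 0.868 | 94.1% | 22 |
| 0.4 | 0.70 | 0.837 | 92.5% | 24 |
| 0.5 | 0.75 | 0.808 | 90.7% | 26 |
| 0.6 | 0.80 | 0.783 | 88.9% | 27 |
| 0.7 | 0.85 | 0.759 | 86.9% | 29 |
| 0.8 | 0.90 | 0.738 | 85.0% | 30 |
| 0.9 | 0.95 | 0.718 | 83.1% | 32 |

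The comparator in every row is 81.2% power, and 34 per group for 80%.

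**5. Simulation at r = 0.6, 34 per group.** Type I error was 4.9% (change score) and 4.7% (ANCOVA). Power was 81.6% and 88.5%.

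**6. Chance imbalance.** The standard error of the baseline mean difference is √(2/34) = 0.24 SD. Given an imbalance of that size, the change-score estimate moves by (1 − r) × 0.24 raw SDs. Dividing by the change SD √(2(1 − r)) gives √((1 − r)/2) × 0.24 change-score SDs. At r = 0.3 this is 0.143, about 20% of the 0.7 target; at r = 0.8 it is 0.077, about 11%; at r = 0.9 it is 0.054, about 8%.

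**7. The other reading of d.** If 0.7 is standardised by the raw HOMA SD, power at 34 per group is 73.8%, 81.2%, 88.9% and 95.6% for the change score at r = 0.4, 0.5, 0.6 and 0.7. ANCOVA gives 87.3%, 90.7%, 94.5% and 97.8%. The direction is the same.

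**The case against.** The planned test is a legitimate analysis and it matches the design: the trial is sized on pre-post differences and the interaction tests that contrast. Its type I error is correct and its power is as stated. Thirty-four per arm is also the pessimistic case. With the roughly 7% loss seen in the team's previous study, 42 × 0.93 ≈ 39 per arm would complete, and the planned test would have about 86% power. All of this stands. The issue is efficiency, not validity or sizing.

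The size of the gain rests on an r that the article does not give. At r = 0.9 it is only about 2 points. That also stands, and is why a range is shown.

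Three stronger readings might be inferred, and the article does not support them.
- That the plan ignores baseline HOMA. It does not: the change score subtracts it. What is missing is an estimated slope.
- That the result would be biased. Under randomisation the change-score estimate is unbiased on average; the shift in step 6 is conditional on an imbalance having occurred.
- That Tanner stage is collected and will never be used. Listing it as a potential confounder is compatible with a planned adjustment, and an article may leave the covariate list to a fuller document. Differencing also removes any effect of sex or Tanner stage that is constant over time, so they help only if they predict change in HOMA.

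The silence on covariates does not dispose of the main point, because the article does fix the method for the treatment effect, and that method is the less efficient one.

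**Conclusion.** The point holds as an improvement in efficiency. As written, the test of exercise on HOMA and the secondary outcomes is a change-score t test. It is valid, and 34 per arm delivers its stated power.

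ANCOVA on the baseline value would raise power from 81.2% to between 83% (r = 0.9) and 94% (r = 0.3), a gain of about 2 to 13 points. It would also remove the shift caused by chance imbalance in the baseline outcome. These sizes assume equal SDs at both visits and d = 0.7 on the change-score SD, and the gain vanishes as r approaches 1.

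The further gain from sex and Tanner stage cannot be computed from the article and may be small. As an illustration only, if they explained 5 to 10% of the residual variance (an assumption), power at r = 0.6 would be about 90 to 92%.

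**What to change.** In the Data analyses plan, for HOMA and each continuous secondary outcome, replace the time × group ANOVA with ANCOVA of the week-22 value on group and the baseline value of the same outcome. Report the adjusted between-group difference with its 95% CI.

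A constrained longitudinal model with a common baseline mean is an alternative. It also keeps children who have only a baseline value, which suits the stated intention-to-treat principle.

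Sex and baseline Tanner stage may be added. If so, name them, and fix the coding of Tanner stage, before the data are analysed.

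The cost is analysis wording and a few degrees of freedom: one for baseline, one for sex, and one or more for Tanner stage depending on its coding. No new data are needed, SPSS (already named in the article) fits the model, and the sample size stays at 42 per group.

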### Data dissemination plan

The principal investigator will inform the parents about their child’s health before and after the intervention program. The main results of the trial will be communicated to the health care professionals (pediatricians) in Vitoria-Gasteiz and other relevant groups (e.g., university academics), as well as to the public. Scientific articles will be also written.

## Discussion

The worldwide obesity pandemic and the increasing prevalence of T2D at younger ages are important public health issues with both individual and social costs. Likewise, research focusing on the prevention of T2D in pre-adolescent children is a high priority for public health. Scientific associations emphasize the need for evidence-based adiposity and IRS control treatments that may reduce T2D risk in children at a high risk [6].

The primary aim of the PREDIKID project is to test the effect of a multidisciplinary program including supervised exercise in the reduction of IRS in pre-adolescents at a high risk to develop T2D that could serve as preventive model of T2D in childhood. The families participating in the study will receive an educational program including lifestyle, psychological and emotional aspects that the scientific literature implicates in the development and progression of obesity and T2D risk in childhood. Moreover, the exercise intervention of the PREDIKID study will obtain objective data about the effect of high intensity exercise on metabolic variables closely associated to T2D risk in children, such as insulin resistance, HbA1c, ectopic fat, total, abdominal and visceral adiposity, cIMT, cardiorespiratory fitness, adipokines, hepatokines and cytokines, blood pressure or lipid profile. We will examine clinical outcomes intimately associated with T2D using innovative technology and reference methods. Likewise, the PREDIKID project will help to better understand the relationship between hepatic and pancreatic fat and IRS and risk of T2D in children. In addition, the current study may offer relevant clinical information about the efficacy of a family based multidisciplinary intervention program that includes exercise on reducing ectopic fat, IRS and cardiovascular disease risk factors in children at a high risk of T2D.

The pathophysiology of childhood obesity and associated comorbidities, such as T2D, is not well established. To date it is not clear why some children develop IRS and T2D, while others show the metabolically healthy phenotype [70]. Biomarkers for early detection of children at risk of T2D would greatly improve the care of children with overweight/obesity. Hence, there is a need to search for clinically relevant markers with prognostic value for intervention success. Recently, miRNAs have been proposed as promising biomarkers in terms of both diagnosis and prognosis of obesity-related comorbidities [71, 72]. The PREDIKID project will help to identify miRNAs potentially associated with early onset of IRS in children with overweight/obesity. Moreover, the differential expression and responses in circulating miRNAs between the control group and the exercise group may help to understand the underlying mechanisms of the effect of exercise on IRS, as well as to predict individual variability to the intervention in overweight/obese children.

### Trial status

The recruitment started on March 2017, and is expected to finish in September 2018.

## Abbreviations

BMI: Body Mass Index
cIMT: Carotid intima-media thickness
HDL: High-density lipoprotein
HOMA: Homeostatic model assessment
HRmax: Maximal heart rate
IRS: Insulin resistance syndrome
LDL: Low-density lipoprotein
miRNAs: MicroRNAs
PREDIKID: Prevention of Diabetes in Kids
T2D: Type-2 diabetes
